#### Clinical Outcomes

Previous CST and iCST research and the Interdem consensus statement on outcome measures for dementia informed the outcome measure selection for this study [22]. Key outcome measures of interest for people with dementia (Textbox 2) are cognition and QoL, as previous CST research has shown improvements in these domains [1]. For carers, the key outcome measure (Textbox 3) is QoL as previous iCST research has shown improvement in the QoL of carers [2]. This study additionally includes technology-related scales to assess the usability and acceptability of the iCST app and computer use self-efficacy (Textbox 4). All assessments will take place in the homes of the participants. Wherever possible, 2 researchers will visit the participants in order to interview the person with dementia and his/her carer separately. It will be possible to conduct the assessments over 2 days in case of fatigue or other practical issues such as lack of time. As in the previous iCST trial, the first follow-up at 5 weeks will be included to safeguard data against loss-to-follow-up [2]. The second follow-up will take place at 11 weeks after the baseline as this should be the point that participants in the experimental group will have completed each activity on the iCST app.

Outcome measures for people with dementia.

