### Statistical Analyses

Key feasibility outcomes will be reported through frequencies and will include the number of participants screened, recruited, randomized, and retained through the duration of the trial. Adherence to the intervention will be assessed by calculating the average number of iCST app activities completed by the dyad logged in the weekly telephone calls. The usability and acceptability of the iCST app will be further investigated by examining data from the weekly telephone calls, posttrial interviews, and by calculating scores on the Questionnaire of Usability and Acceptability, with higher scores indicating higher levels of usability and acceptability. Data from the posttrial interviews will be coded and summarized and may be analyzed thematically with specialized software if sufficient data have been obtained to reach data saturation [35]. Lastly, outcome measures will be assessed for appropriateness by calculating missing data rates within the measures and across the follow-ups. As this is a feasibility trial and null hypothesis significance testing is inappropriate due to a likely lack of power to detect significant effects of the intervention [36-38], analyses will mainly include descriptive statistics computed for each group and outcome measures, including means, standard deviations, 95% confidence intervals, and effect sizes [12,39]. However, in order to compare the outcomes on each of the questionnaires between the 2 groups, an analysis of covariance will be undertaken, which will help to better understand any trends in the data. All analyses will be based on the intention-to-treat principle in that all available data will be included in the analyses. Rules for missing data will be adapted from the main iCST trial [2]. Data will not be imputed if outcome measures or assessments are missing in full, and imputation (using prorating) will only be used when fewer than 20% of cases are missing on any given measure.

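### The 5-week visit is meant to guard against loss to follow-up, but under the stated analysis it does not inform the 11-week comparison for dyads lost after week 5 (minor)

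*Protocol article*

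**What the plan says.** All statements are in the Methods of the protocol article.

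- **Purpose of the 5-week visit (Clinical Outcomes).** The only reason given is that "the first follow-up at 5 weeks will be included to safeguard data against loss-to-follow-up", following the earlier iCST trial.
- **Final visit (Clinical Outcomes).** "The second follow-up will take place at 11 weeks after the baseline", chosen because every app activity should have been completed by then.
- **Between-group model (Statistical Analyses).** "in order to compare the outcomes on each of the questionnaires between the 2 groups, an analysis of covariance will be undertaken". Neither the visit nor the covariates are named.
- **Analysis set (Statistical Analyses).** "All analyses will be based on the intention-to-treat principle in that all available data will be included in the analyses".
- **Missing data (Statistical Analyses).** "Data will not be imputed if outcome measures or assessments are missing in full". Prorating is the one method of filling in that is allowed, below a 20% threshold. It fills gaps within a measure that was partly completed. It cannot supply a visit that did not take place.

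The same section plans mainly descriptive statistics, regards significance testing as inappropriate here, and will report missing-data rates across the follow-ups.

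**The concern.** An interim visit protects an endpoint against dropout only if the analysis lets the interim score speak for the missing final score. That takes a joint model of the two visits, an imputation step or a carry-forward rule. The article names none of these, and its rule on wholly missing assessments excludes imputation. The reason given for collecting week-5 data is therefore not carried through to the 11-week comparison. It also fits poorly with describing the analysis as intention-to-treat on all available data, since some available follow-up data have no route into that estimate.

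At stake are the adjusted 11-week differences and their intervals. If app users doing badly at week 5 leave and control dyads doing badly do not, those who remain flatter the app. If loss is unrelated to outcome, some precision is given up that data already in hand could partly restore.

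**Working it through.** **1. What each dyad contributes under the stated rules**

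| Dyad seen at | Week-5 descriptives | Week-5 ANCOVA, if run | Week-11 ANCOVA |
|---|---|---|---|
| Baseline, week 5, week 11 | yes | yes | yes |
| Baseline, week 5 only | yes | yes | no |

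The last cell is no whether ANCOVA is run at week 11 only or at each visit. A single-visit ANCOVA needs the week-11 score, and a wholly missed assessment is not imputed.

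**2. The plan's own figure**

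The Sample Size section gives 60 dyads, 30 per arm: 2 × 30 = 60, which agrees. There is no power calculation, expected dropout, SD or correlation to reproduce. Every dropout rate and correlation below is an assumption, shown as a range.

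**3. Precision when loss is unrelated to scores**

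Let n = 30 per arm, d the share missing week 11, and r the week-5 to week-11 correlation after adjusting for baseline. In large samples:

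- completer ANCOVA has variance proportional to 1/[n(1 − d)]
- a likelihood analysis using both visits has variance proportional to (1 − r²d)/[n(1 − d)]
- effective n per arm for the latter is n(1 − d)/(1 − r²d)

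| d | Completers per arm | Effective n, r = 0.5 | Effective n, r = 0.8 | Fall in SE |
|---|---|---|---|---|
| 10% | 27.0 | 27.7 | 28.8 | 1% to 3% |
| 20% | 24.0 | 25.3 | 27.5 | 3% to 7% |
| 30% | 21.0 | 22.7 | 26.0 | 4% to 10% |

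Example: d = 20%, r = 0.8 gives 24/(1 − 0.64 × 0.2) = 24/0.872 = 27.5, and √0.872 = 0.934, a fall of about 7%.

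r is a partial correlation. If the plain correlation ρ is the same between all three visits, then r = ρ/(1 + ρ). For ρ = 0.6 to 0.8 that is 0.375 to 0.444, and at d = 20% the SE falls by only about 1% to 2%.

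**4. Bias when loss depends on the week-5 score**

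Simulations used 30 per arm, 4,000 trials per scenario and no true effect. Bias is in outcome SDs, and positive values favour the app.

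*About 20% lost, app-arm loss driven by poor week-5 scores:*

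| ρ between visits | Completer ANCOVA bias | Joint-model bias | Empirical SE, ANCOVA v joint |
|---|---|---|---|
| 0.6 | 0.055 | −0.004 | 0.232 v 0.231 |
| 0.7 | 0.051 | −0.002 | 0.210 v 0.208 |
| 0.8 | 0.046 | 0.005 | 0.178 v 0.175 |

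A separate run with 20% to 22% lost gave ANCOVA biases of 0.060, 0.052 and 0.041, and joint-model bias of 0.002 or less in absolute size.

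*About 10% lost at random in the control arm, 33% lost in the app arm depending on week-5 score:*

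| r (baseline-adjusted) | Completer ANCOVA bias | Joint-model bias | Empirical SE, ANCOVA v joint |
|---|---|---|---|
| 0.5 | 0.075 | 0.004 | 0.214 v 0.209 |
| 0.7 | 0.101 | 0.003 | 0.209 v 0.198 |
| 0.8 | 0.117 | 0.005 | 0.212 v 0.195 |

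*Same dependence on week-5 score in both arms, about 20% lost:* completer ANCOVA bias was −0.002, 0.003 and −0.001 at ρ = 0.6, 0.7 and 0.8, which is zero within simulation error.

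**5. Bias relative to noise**

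In the first scenario, 0.055/0.232 = 0.24 and 0.046/0.178 = 0.26, about a quarter of a standard error. In the second, 0.075/0.214 = 0.35 and 0.117/0.212 = 0.55, about a third to a half.

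**The case against.** The strongest reply is that the article nowhere promises to protect the 11-week estimate. It speaks of safeguarding data, and having post-baseline scores on dyads who later leave does that literally. The ANCOVA visit is unstated, so week-5 scores may well be compared between arms, and they will appear in the descriptive statistics. A reader might infer that week-5 data are thrown away. The documents do not support that, nor that nothing is imputed, since prorating is allowed for partly completed measures. These corrections stand. They leave untouched that the 11-week estimate takes nothing from week 5 under either reading of the ANCOVA.

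It can also be said that visit and covariates belong in an analysis plan that is not shown. That is fair for those details. The point here is narrower: the article itself fixes the model and the rule on missed assessments, and together they leave the visit's stated purpose unserved at week 11.

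Two further readings go too far. One is that completer ANCOVA is unbiased only if loss is unrelated to the week-5 score. It is also unbiased when that dependence is the same in both arms and there is no true effect, as the third scenario shows. The other is that the pandemic shows the bias at work. Assuming uniform accrual of 61 dyads over the 516 days from 1 November 2018 to 31 March 2020, and no visits afterwards, 61 × 42/516 ≈ 5 dyads would be past week 5 but short of week 11. That would be administrative loss with no evident link to scores, so it costs precision and does not demonstrate bias. The article reports no missed visits.

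Lastly, the stakes are limited. The aim is usability and feasibility, the stated feasibility benchmark is adherence, and ANCOVA serves only to look at trends. Nothing in the article says the effect estimates will be used to design the full trial. This stands and sets the weight of the point.

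**Conclusion.** The point holds in limited form. The 5-week visit has a stated protective purpose that the stated analysis does not deliver for the 11-week between-group estimate, which is completer-only.

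The consequence is small. With loss that depends on week-5 scores in the app arm, the bias is about 0.05 SD at about 20% loss and about 0.08 to 0.12 SD at 10% against 33% loss, beside a standard error near 0.2 SD. With loss unrelated to scores, or acting alike in both arms under no true effect, the cost is a standard error up to about 10% larger than necessary at the extreme of the assumed range, and often only 1% to 2%. All of this rests on assumed dropout rates, correlations and mechanisms. The documents supply none, and they do not suggest that dropout actually differs by arm.

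It is a cheap improvement to a secondary comparison in a mainly descriptive feasibility trial, not a threat to the trial's conclusions.

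**What to change.** For each outcome measured at both follow-ups, fit one likelihood-based repeated-measures model:

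- responses: the 5-week and 11-week scores
- fixed effects: baseline score, arm, visit, arm-by-visit and baseline-by-visit
- covariance: unstructured across the two visits
- analysis set: all randomised dyads with at least one follow-up, in the arm to which they were randomised

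Report the 11-week adjusted difference with its 95% CI, and keep the completer ANCOVA as a sensitivity analysis, stating its visit. Measures not taken at both follow-ups, such as the usability questionnaire, fall outside this model.

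The cost is analysis syntax only. No new data are needed, and the SPSS version already named has a MIXED procedure. The downside is a slightly more complex model. It relies on loss being explained by baseline, arm and week-5 score, and it does not help with dyads who have no follow-up at all. If the ANCOVA is preferred, the alternative is to name its visit or visits and restate why the 5-week visit is collected.

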**Measures**
Cognition measured using the Alzheimer’s Disease Assessment Scale-Cognitive Subscale [23].Quality of life measured using the Quality of Life-Alzheimer’s Disease (QoL-AD) questionnaire [24]. Carers will complete the family version of the QoL-AD.Health-related quality of life measured using the EuroQoL 5-dimension questionnaire [25].Relationship quality measured using the Quality of the Carer-Patient Relationship questionnaire [26].Symptoms of depression measured using the Cornell Scale for Depression in Dementia [27]. Carers will complete this questionnaire as an informant.Behavioral disturbances measured using the Neuropsychiatric Inventory and will be rated by the carer only [28].Functional abilities measured using the Bristol Activities of Daily Living Scale [29] and rated by the carer only.

Outcome measures for carers.
**Measures**
Health-related quality of life measured using the EuroQoL 5-dimension questionnaire [25].Anxiety and depression measured using the Hospital Anxiety and Depression Scale [30].Relationship quality measured using the Quality of the Carer-Patient Relationship questionnaire [26].

Technology scales for people with dementia and carers.
**Scales**
Self-efficacy beliefs in computer/tablet use measured at baseline only using the Computer User Self-Efficacy scale [31].Usability and acceptability of the individual cognitive stimulation therapy app measured at the second follow-up and in the experimental group only by using the Questionnaire of Usability and Acceptability [32].

### Posttrial Interviews

A small proportion of dyads in the experimental group will be invited to participate in joint semistructured interviews. The purpose of the interviews is to gain additional information on the layout and content of the iCST app, the overall experience of using it as a dyad, and any practicalities surrounding its use in daily life. The interview serves as a complementary data collection method to the weekly telephone support calls and the usability questionnaire, as a semistructured interview generates more in-depth data that otherwise cannot be accessed through quantitative methods only [33]. A discussion guide will be developed, including the key areas mentioned before, to help guide the interview. Each dyad in the experimental group will be invited to participate in the interview upon completion of the study. If they are interested, further details for the person with dementia and carer will be sent. If a dyad agrees to participate, a date for the interview will be set. All interviews will take place in the home of the participants. Written informed consent will be obtained from both participants by the unblinded researcher. The data will be audio-recorded, transcribed, and subsequently stored on a password-protected computer at the University of Nottingham.

### End of Study

The second follow-up constitutes the end of the study for participants. At this final visit by the blinded researcher, all participants will be given a £10 (US $13.01) App Store or Google Play store voucher in order for them to download the iCST app once it has been released on the app stores. This will be accompanied by an instructional document on how to redeem the voucher and a newsletter containing information on what will happen next, such as making improvements to the app and analyzing and disseminating the results.

### Ethical Considerations

Ethical approval has been obtained from the Yorkshire and the Humber-Bradford Leeds Research Ethics Committee and NHS Health Research Authority in March 2018 (reference number 17/YH/0405).

### Consent

People with mild-to-moderate dementia will be recruited in the study and are expected to be able to give informed consent for participation, provided that appropriate care is taken in explaining the research and sufficient time is allowed for them to reach a decision. Written informed consent will be taken at baseline from both the person with dementia and the carer. Since the intervention requires joint participation, it is likely that both participants will consult each other in making their decision. Therefore, it is possible that any individual participant’s decision to either participate or not participate with the research may be influenced by the other participant. However, it is important that individual participants are not forced to make a decision against their will and the researcher will spend as much time as necessary in speaking to the participants individually about the research. It will be made clear to both people with dementia and carers that no disadvantage will accrue in terms of the current care they receive or any future research opportunities if they choose not to participate or withdraw from the study. The consent form will be signed and dated by the participant and the researcher before they enter the study. One copy will be given to the participant and one will be retained at the local study site.

### Adverse Events

Previous work with CST, maintenance CST, and iCST has not documented any harmful side effects nor any serious adverse events from participating in the intervention activities [1,2,34]. Given that the iCST app is based on the principles of CST and follows a comparable structure to iCST, it is expected that this study will not lead to harmful side effects for either the person with dementia or the carer. Researchers will be made aware of any adverse events during follow-up assessments or the weekly telephone support calls. The trial manager and chief investigator of the study will be informed in case of any adverse events, and they will assess the severity of the adverse event. Serious adverse events include death, illness related to a previous health condition, or hospitalization.

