**Methods:**

We aim to recruit 60 people with mild-to-moderate dementia and their informal carers as dyads in a multi-center feasibility RCT with a treatment-as-usual control group. Both parties must be able to provide informed consent and participate in the intervention. Dyads will complete a baseline assessment that will include cognition and quality of life measures and they will subsequently be randomized (1:1) to the iCST app intervention in addition to usual care or to usual care only. All participants will be followed up at 5 weeks and at 11 weeks after the baseline assessments. A range of feasibility outcomes will be assessed, including recruitment and retention rates, intervention fidelity and usability, and acceptability of the outcome measures. A sample of the experimental group will be invited to a semistructured posttrial interview to further examine the experience of using the iCST app.

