#### Blinding

This trial will include both blinded and unblinded researchers at each local site. It is not possible to blind the participants to their treatment arm as the iCST app is a nonpharmacological intervention. However, each study site will include at least one researcher kept in ignorance of study allocations. The baseline assessment can be performed by either researcher. However, both follow-ups will be completed only by the researcher who is unaware of the randomization outcome for each dyad. If disclosure does occur, this will be recorded by the visiting researcher along with details on how it occurred. The unblinded researcher will perform the randomization, communicate the outcome with the participants, and for the experimental group, install the iCST app, provide weekly telephone support calls, and complete the usability and acceptability questionnaire at the end of the study. Furthermore, the unblinded researcher will not be informed about the results of the assessments.

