### iCST App Intervention

Participants in the experimental group will use the iCST app (prototype v3.0) over 11 weeks after the baseline assessments. The content of the app was modified from the paper-based iCST manual, including the principles, themes, and activities [2], and was based on consultations and qualitative research with people with dementia, carers, and the software development company [11]. The iCST app is a one-to-one, carer-led, home-based program of structured cognitive stimulation for people with dementia but delivered on a touchscreen tablet. It includes 21 activities consisting of both game-like interactive features such as audio-visual stimuli and discussion questions (Table 1). These activities offer mental stimulation not only through the content on the app but also through conversation.

**Table 1 table1:** List of the individual cognitive stimulation therapy app activities (prototype v3.0).

Type of activity	Activity name
Games only	Being Creative Spaceman Trivia Quiz Word Search Sudoku Being Active Brainstorm
Discussion questions only	Past Events Useful Tips My Life Arts Old Wives’ Tales Toys Are Us
Games and discussion questions	Sounds Odd one Out The Price is Right Globe Trotter Food In Pairs Sayings ISpy

In addition, this app includes several other features such as a short introduction section explaining the background and key tips for using the app, a home screen that features completed activities, and a choice of 2 levels. Level 2 contains either more challenging content or different questions from Level 1, and it is up to the participants to determine which level they feel more comfortable with for each activity. Figure 2 contains screenshots of the iCST app. Considering previous CST and iCST research and findings from the development work, it is recommended that participants use the app for 2 or 3 times a week for 30 minutes [2]. Participants are free to spend more time on the app if they wish, and this will be recorded during the weekly telephone calls.

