### Training and Adherence

In order to ensure treatment integrity for all participants, individual study sites will receive a demonstration of the iCST app along with training in its installation and use prior to the start of recruitment. Dyads in the experimental group will receive an in-home visit from the unblinded researcher who will install the app and explain how it works using a short supplementary document containing instructions with screenshots of the app. Furthermore, all dyads will receive weekly telephone support calls from the same unblinded researcher in order to monitor adherence and to track the overall progress and any challenges or technical difficulties with using the iCST app. Phone calls will be completed with the carer and all questions will be included on a standardized telephone sheet. The questions relate to general experience, number of sessions completed in a week (on average), amount of time spent per session (on average), enjoyment, and any likes/dislikes. Any reason for not being able to use the iCST app over the week will also be recorded on the telephone sheet.

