### TAU Group

The control group will consist of the TAU group and will not receive any additional interventions. TAU groups are typically used to compare experimental interventions to care, which participants already receive in practice [19]. Therefore, the TAU control group will enable us to compare the effects of the iCST app with the natural progression of people with dementia under conditions of usual care. The treatments and services that are already available to people with dementia and their carers randomized to the TAU control group may differ between and within recruitment sites, for instance, regarding acetylcholinesterase inhibitors or being involved in some form of cognitive stimulation already. However, it is unlikely that people have access to computerized versions of iCST since these do not exist, to the best of our knowledge. The visiting researcher will record any current participation with CST groups and use of acetylcholinesterase inhibitors at the baseline assessment.

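### Adverse events are gathered through visits or weekly calls, and the calls appear to go to the app arm only, so a pooled count by arm would be uneven; changes in usual care after baseline are not described

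*Protocol article*

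**What the plan says.** Adverse Events names two routes by which events come to light: "Researchers will be made aware of any adverse events during follow-up assessments or the weekly telephone support calls". They then go to the trial manager and chief investigator, who assess severity.

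Three sections bear on who is telephoned. Blinding lists the unblinded researcher's tasks, among them "for the experimental group, install the iCST app, provide weekly telephone support calls". TAU Group says: "The control group will consist of the TAU group and will not receive any additional interventions". Training and Adherence says that "all dyads will receive weekly telephone support calls from the same unblinded researcher in order to monitor adherence".

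Visits are the same in both arms. The Abstract (Methods) states: "All participants will be followed up at 5 weeks and at 11 weeks after the baseline assessments". Blinding assigns both follow-ups to a researcher who does not know the allocation. The length of app use is given under iCST App Intervention: "Participants in the experimental group will use the iCST app (prototype v3.0) over 11 weeks after the baseline assessments".

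On co-treatment, TAU Group accepts that usual care may vary between and within sites, including drug treatment and existing cognitive stimulation. It then says: "The visiting researcher will record any current participation with CST groups and use of acetylcholinesterase inhibitors at the baseline assessment". The article mentions no later recording.

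**The concern.** When one arm is contacted more often, more of its events are heard of, even if the true rates are equal. If visit reports and call reports are added together and shown by arm, a harmless app can look as if it causes events. Conversely, a real excess can be dismissed as an effect of closer contact. The two routes also differ in who listens: the calls are made by the unblinded researcher and the follow-up visits by the blinded one.

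The co-treatment issue is separate and smaller. The TAU arm is meant to show progression under usual care, and the trial is meant to inform the design of a full-scale RCT. If CST attendance and inhibitor use are noted once, before randomization, the article's data cannot show whether usual care changed over the 11 weeks, or whether it changed differently in the two arms of an open-label study.

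**Working it through.** **Step 1: who is called.** The three sections cannot all stand as written. Blinding limits the calls to the experimental group and TAU Group rules out anything additional for controls, while Training and Adherence says all dyads. The context of that last statement favours the app-only reading. The preceding sentence is about experimental-group dyads, and the purpose of the calls (adherence, progress, technical difficulties with the app) and the listed questions make sense only for app users. The rest of the check takes that reading. If controls are called too, the imbalance in Step 2 disappears, and Blinding and TAU Group need correcting instead.

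**Step 2: occasions for reporting.**
- App arm: 11 weekly calls (an upper bound over 11 weeks) + 2 visits = 13.
- TAU arm: 2 visits.
- Longest gap between contacts: about 1 week in the app arm; in TAU, 5 weeks to the first visit and 11 − 5 = 6 weeks to the second.

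**Step 3: how large the distortion could be.** The article gives no event rate and no recall figure, so everything in this step is assumed and shows a range only.

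(a) Simple version. Suppose the true risk is 20% in both arms, calls catch every event, and visits alone recover 50% to 80%.
- App arm reports 20%. TAU reports 0.20 × 0.5 = 10% to 0.20 × 0.8 = 16%.
- Ratio: 0.20/0.16 = 1.25 to 0.20/0.10 = 2.0.
- With 30 dyads per arm: 6 against 3 to 4.8 dyads, a gap of 1.2 to 3.

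(b) Recall-decay version. Suppose events are uniform over 11 weeks and the chance of being reported halves for every *h* weeks until the next contact. The mean share reported over a gap of *g* weeks is (h / (g ln 2)) × (1 − 2^(−g/h)). The app arm has *g* = 1 throughout; TAU is the average over gaps of 5 and 6 weeks, weighted by length. For *h* = 4:
- App: (4/0.693) × (1 − 0.841) = 0.918.
- TAU: (4/0.693) × [(1 − 0.420) + (1 − 0.354)] / 11 = 0.643.
- Ratio: 0.918/0.643 = 1.43.

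| Half-life of recall *h* (weeks, assumed) | App share reported | TAU share reported | Ratio |
|---|---|---|---|
| 2 | 0.845 | 0.445 | 1.90 |
| 4 | 0.918 | 0.643 | 1.43 |
| 8 | 0.958 | 0.794 | 1.21 |
| 16 | 0.979 | 0.889 | 1.10 |

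Both versions point the same way, towards more reports in the app arm. The ratio approaches 1 for events that are not forgotten.

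**Step 4: co-treatment.** TAU Group names two items and one time point, baseline. Neither the outcome lists nor Statistical Analyses mentions a second recording. From what is described, baseline co-treatment can be compared between arms; change after randomization cannot.

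**The case against.** A reader might infer that neither harms nor co-treatment can be compared between the arms at all. The article does not support that. Both arms have the same blinded visits at weeks 5 and 11, and follow-up assessments are a named route for adverse events. A like-for-like comparison is therefore available if the source of each report is kept. Baseline co-treatment is comparable too.

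Several further objections carry weight:
- No between-arm test of harms is planned. The aims are feasibility and usability, the analysis is mainly descriptive, and the between-group model is an ANCOVA on the questionnaires. Closer safety contact in the arm receiving a prototype is reasonable for notification purposes. This limits the point to how any adverse-event table by arm is built and read.
- Baseline-only recording is partly inferred from silence. Where the authors mean baseline only they say so, as for the computer self-efficacy scale, and the full protocol or case report forms may add later recording.
- A reader might call new CST attendance or a new inhibitor in the TAU arm contamination. It is not. Usual care is defined to include such treatments, and they can start in either arm. Contamination would mean controls obtaining the app, which the article considers unlikely.
- The listed call questions contain no adverse-event item, so it is doubtful that calls catch every event, as version (a) assumes. Deaths and hospitalizations are unlikely to be forgotten within 5 to 6 weeks.
- The wording on all dyads may be only a slip.

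What remains is that the Adverse Events section, followed as written, mixes two routes of which one appears open to a single arm, and nothing in the article says the source will be kept apart.

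**Conclusion.** The point holds as a modest, inexpensive improvement. The statements on who receives calls conflict and must be reconciled. On the reading that Blinding and TAU Group support, reporting occasions are up to 13 against 2, and a pooled adverse-event count by arm would be biased towards more reported events in the app arm. The direction follows from the design provided that some events are forgotten or left unmentioned by the next visit. The size is unknown: the 1.1 to 2.0 range rests wholly on assumed recall, and the distortion is likely small for death or hospitalization. Changes in usual care after randomization, in either arm, would not be described by the data the article sets out, unless the full protocol provides for later recording.

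**What to change.** 1. Reconcile Training and Adherence with Blinding and TAU Group, so that one statement says who receives the weekly calls.
2. At the blinded 5- and 11-week visits, ask both arms one identical question about all adverse events since the last visit, whether or not already reported to the study. Word it without reference to the app or the calls, so that it does not prompt disclosure of the allocation.
3. At the same visits, repeat the baseline co-treatment items (CST participation, acetylcholinesterase inhibitor use) in both arms.
4. Record the source of every adverse-event report. Base any between-arm table on visit-elicited reports and list call-reported events separately for the app arm.

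The article reports that data collection was completed in March 2020, so items 2 and 3 can serve only the full-scale trial. For the present report, tabulate events by source, and state that co-treatment changes were not captured if that is so.

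The cost is a few minutes per visit and a change of wording. Some events mentioned only by telephone will drop out of the between-arm table, though they stay in the separate list. A carer who has already reported an event by telephone may still not repeat it at the visit; the wording in item 2 reduces this but may not remove it.
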